## Abstract

**Background:**

Due to multiple and interacting factors, Latino children are disproportionately at risk for overweight and obesity in the United States. Childhood obesity increases the risk for adverse physical and psychosocial outcomes throughout the lifespan. Intensive behavioral interventions recommended in primary care settings may not conform to current practices, and the most vulnerable populations are often unable to access these services. Community Health Workers (CHWs) off**e**r a promising approach to bridging the gap between vulnerable communities and culturally competent services. La Vida Buena (The Good Life) is an 8-week family-focused intervention for Latino children 5–8 years old and their parents or caregivers who are patients at a Federally-Qualified Community Health Center (FQHC). It is a culturally and linguistically appropriate curriculum, facilitated by CHWs, that targets family behaviors to foster a healthy lifestyle in order to prevent and mitigate childhood overweight and obesity.

**Methods:**

The primary objective is to test the effectiveness of the La Vida Buena (LVB) childhood obesity program among Latino children 5–8 years old and their families as compared with a single educational session. This study uses a parallel two-arm quasi-experimental design. The intervention group receives the 8-week La Vida Buena intervention and the comparison group receives a single educational session. The primary outcome is the change in the child’s BMI z-score from baseline to 6 months.

**Discussion:**

The implementation and evaluation of La Vida Buena may inform research and practice for linking Latino patients in FQHCs to culturally responsive community-based childhood obesity interventions. It will also contribute to the literature about CHWs as facilitators of behavior change for families underserved by health services and preventive programs. La Vida Buena can serve as a culturally and linguistically appropriate early intervention curriculum that will foster a healthy home environment for childhood obesity mitigation and prevention.

**Trial registration:**

The trial was retrospectively registered on December 18, 2018. The ClinicalTrials.gov Identifier is NCT03781856.

## Background

The Latino population bears a significant burden of overweight and obesity in the United States. The prevalence of obesity in Latino adults is 47%, as compared with 39.8% for adults overall and 37.9% of non-Hispanic white adults. This trend appears to be initiated in childhood; the prevalence of obesity among Latino youth is 25.8%. as compared with 18.5% overall, and 14.1% for non-Hispanic white youth [1].

Childhood obesity is associated with adverse physical and psychosocial outcomes that carry into adulthood. Childhood and adolescent overweight and obesity are associated with poorer health status, lower emotional functioning, and worse educational performance [2–4]. Children with obesity are more likely to experience psychosocial issues such as anxiety, depression, low self-esteem and bullying [3, 5]. Children with obesity are likely to become adults with obesity [6], and their health issues tend to be more severe as adults [7–9]. Obesity is associated with a variety of serious health conditions, including hypertension, type 2 diabetes, heart disease, stroke and cancer [8–10].

Importantly, the major risk factors for childhood overweight and obesity include modifiable environmental and behavioral factors. Family behaviors such as eating calorie dense and nutrient-poor foods, drinking sugar-sweetened beverages, not getting enough physical activity, not eating together, not sleeping enough and spending too much time doing sedentary activities all contribute to excess weight gain [9]. For Latino families in particular, home environment factors such as parental influences, screen time, sedentary activity, food security and sleep duration are associated with childhood obesity [11]. Broader environmental and policy factors such as the affordability and accessibility of healthy foods, marketing and promotion, community design, school environment and availability of safe physical activity spaces further shape individual and family behaviors that impact obesity [12].

The CDC defines childhood overweight as a BMI at or above the 85th percentile for children of the same age and sex, and obesity as a BMI at or above the 95th percentile [7]. The US Preventive Service Task Force recommends that clinicians measure children’s height and weight and refer children with overweight or obesity to comprehensive, intensive behavioral interventions [13]. Successful interventions include over 26 contact hours, family involvement, and multidisciplinary facilitation teams composed of clinicians, dietitians and social workers [13]. However, these recommendations are misaligned with current practices in many primary care environments, and they do not necessarily reach the populations most in need of intervention [14]. A systematic review of recruitment and retention in obesity prevention trials targeting minority or low-income children found that retention rates were lower for trials that only targeted Latinos, involved children and parents, focused on overweight or obese children, were community-based, or included both nutrition and physical activity [15].

Community Health Workers (CHWs), frontline public health workers with a unique connection to the community served, offer a promising approach to engage and execute health promotion efforts with Latino populations [16].CHWs can serve as culturally competent mediators between communities and health service providers. Numerous studies have documented the effectiveness of community-based CHW programs in improving maternal and child health outcomes [17–19] as well promoting the prevention and management of chronic diseases [20, 21].

There is a small but growing body of research exploring the effectiveness of CHW-led childhood obesity programs. CHW-led childhood obesity programs have been implemented in home settings [22, 23], through schools [24] and at an urban health center [25]. These interventions demonstrate that a culturally competent program facilitated by a CHW can be effective in promoting healthy diet and physical activity habits in Latino populations.

This study protocol describes La Vida Buena (The Good Life), a childhood obesity intervention developed by an FQHC in a rural county along the US-Mexico border. The 8-week family-focused program, co-developed and facilitated by CHWs, aims to address childhood obesity in Latino children 5–8 years old and their families who are patients at the Federally Qualified Community Health Center (FQHC). The curriculum is guided by the socio-ecological framework [10, 26] and focuses on behavior change to foster healthy home environments and connection to community resources. The intervention includes activities related to physical activity and nutrition aimed at fostering healthier family habits.

### Objectives

The research study’s primary objective is to test the effectiveness of the 8-week, CHW-led La Vida Buena childhood obesity program among Latino children 5–8 years old and their families as compared with a single educational session.

### Research design and setting

#### Trial design

This is a parallel two-arm quasi-experimental behavioral trial based in two communities.

#### Study setting

The study takes place in two communities in a low-income, rural county along the US-Mexico border. The majority (83%) of residents are Latino, primarily of Mexican origin. Nearly a quarter (24%) of residents live below 100% of the federal poverty level and over a third (35%) of children live in poverty [27, 28] A third of residents (35%) are foreign-born and 81% use a language other than English at home. The county is designated as a Health Professional Shortage Area by the Health Resources and Services Administration [29].

The FQHC that developed and is leading the intervention is the medical home for 91% of all children aged 0–19 in the county, and acts as the county health department. Thirty percent of the FQHC’s pediatric patients have a documented BMI greater than the 85th percentile, exceeding the threshold for childhood overweight/obesity. The Community Health Services Department at the FQHC developed the La Vida Buena curriculum, which is offered offsite in a community setting.

#### Justification for study comparators and design

The study population includes patients from two of the FQHC’s four clinics: the comparison group is drawn from patients in a satellite clinic 10 miles from the intervention community. The patient populations of the two communities are demographically similar. After outcome data collection is complete, the comparison group will have the opportunity to participate in the full intervention.

Our rationale for a quasi-experimental study design takes into account the realities of an FQHC in a rural setting. Randomization would be awkward with a project in which pediatricians are referring their patients, and it would be uncomfortable for CHWs and medical staff to explain and justify random assignment to parents. Group-based randomization was not possible because the FQHC has too few clinics. The use of a comparison group from a different clinic site with a similar demographic profile is a practice-based research design that affords key evidence for other FQHCs that wish to adopt and evaluate the intervention [30].

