#### CBPR approach

This study uses a Community-Based Participatory Research (CBPR) approach fostered by over 20 years of academic-community partnership between the FQHC and their academic partners at a nearby university [31]. CBPR is the co-construction of research through partnerships between researchers and the people affected by, or responsible for, action on the issue under study. Some of the benefits of participatory approaches include the creation of culturally and logistically appropriate research, enhanced recruitment, increased stakeholder capacity, improved sustainability of project goals, and greater potential for systems change [32, 33].

The collaborative and participatory evaluation methods in La Vida Buena includes engagement of a community advisory board (CAB) and a participant advisory board (PAB). The CAB provides support for project development, resources, recruitment and intervention activities. The CAB includes partners from organizations throughout the county, including a biking nonprofit, representatives from local schools, the cooperative extension, and the local farmer’s market. The participant advisory group (PAB) is comprised of parents who have completed the program and who provide the perspective of parents with young children in project planning and dissemination.

Both the CAB and the PAB are active in community- and systems-change activities to complement the emphasis on family behavior change in La Vida Buena. It is essential to integrate clinical and community systems to address childhood obesity [16]. The La Vida Buena team works with the CAB and PAB to identify systems and policy changes that foster a healthy environment in the county.

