#### Primary analysis

The primary endpoint will be change BMI z-score from baseline to 6 months follow up among subjects participating in the program La Vida Buena compared to those receiving an educational class. BMI z-scores will be modeled using an analysis of covariance (ANCOVA) model. Let BMI_*ijk*_ represent the BMI z-score for the *j*^*th*^ subject in the *i*^*th*^ treatment group at the *k*^*th*^ time point for *k* ∈ {0, 1, 2}. The *k* levels for time point correspond to baseline (k = 0), 3 months follow up (k = 1), and 6 months follow up (k = 2). The ANCOVA model is specified as,$$ {\mathrm{BMI}}_{ij2}={\mathrm{BMI}}_{ij0}+{T}_i+{\epsilon}_{ij2} $$where *T*_*i*_ is the intervention effect for and *ϵ*_*ij*2_ is the error term. The effect *T*_*i*_ will be tested at the *α* = 0.05 significance level and the effect size along with a 95% confidence interval will be reported.

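### With one clinic per arm, the term labelled the intervention effect is programme effect plus clinic difference, and its test and 95% CI count child-level variation only

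*Protocol article*

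**What the plan says.** The Trial design section of the protocol article states: "This is a parallel two-arm quasi-experimental behavioral trial based in two communities". Under Justification for study comparators and design it adds: "The study population includes patients from two of the FQHC’s four clinics", and "the comparison group is drawn from patients in a satellite clinic 10 miles from the intervention community". The Comparison group section agrees that the comparator comes from a single satellite clinic.

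The same justification section gives reasons for not randomising individual families, and then says: "Group-based randomization was not possible because the FQHC has too few clinics". On comparability it says: "The patient populations of the two communities are demographically similar". It gives no figures by clinic.

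Under Primary analysis, the model has three parts: baseline BMI z, a treatment term T and a subject-level error. T is defined by the words "is the intervention effect for and" (the sentence is incomplete in the article). It is tested at 0.05 and reported with a 95% confidence interval. The Sample size section uses child-level variation only.

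The Objectives section sets a test of programme effectiveness against a single session as the primary aim. The justification section says the design yields important evidence for other health centres, and the Discussion looks ahead to the programme being shown to work. None of these sections says that clinic and treatment cannot be told apart.

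**The concern.** Arm and clinic are the same variable. Whatever makes 6-month BMI z differ between the two clinics, given baseline, enters T together with the programme effect. Baseline adjustment deals with differences in starting BMI z. It does not deal with a different course over the following six months.

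The standard error of T comes from variation between children, so the clinic contribution is counted as exactly zero. A p-value below 0.05, or an interval that excludes zero, would then be read as evidence about the programme with a precision that holds only if the two clinics would have followed the same course without it. At stake is the interpretation of the primary result, both for this trial and for the other health centres it is meant to inform.

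**Working it through.** **Inputs from the Sample size section:** difference 0.2 z, SD 0.4, type I error 5%, power 80%, 25% attrition, 100 children per site. The SD is described as one in group differences, which is ambiguous; I read it as the residual SD. The test is taken as two-sided. Differences are given as absolute size.

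**The plan's own figure.** The normal formula gives 63 per arm for 0.2 and SD 0.4. Dividing by 0.75 gives 84 per arm, 168 in total (172 with the t distribution). The stated 200 does not reproduce, but it errs on the safe side: 75 completers per arm give about 86% power. The point here does not depend on this.

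**Planned precision.** Completers per arm = 100 × 0.75 = 75. SE = 0.4 × √(2/75) = 0.0653. CI half-width = 1.96 × 0.0653 = 0.128 z.

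**Can the trial estimate clinic variation?** Degrees of freedom between clinics within arms = 2 clinics − 2 arms = 0. Recruiting more children, adding a clinic random effect or using a cluster-robust SE cannot supply what is missing.

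**Size if clinic effects are treated as random.** The documents give no between-clinic SD, so the values of τ below are assumptions. Total SE = √(0.0653² + 2τ²). Type I error of the planned test = 2 × [1 − Φ(1.96 × 0.0653 / total SE)].

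| Assumed τ (z) | Total SE | Half-width, 1.96 × total SE | Type I error |
|---|---|---|---|
| 0 | 0.065 | 0.128 | 5% |
| 0.03 | 0.078 | 0.153 | 10% |
| 0.05 | 0.096 | 0.189 | 18% |
| 0.08 | 0.131 | 0.256 | 33% |

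The same calculation by intraclass correlation uses τ² = 0.16 × ICC/(1 − ICC). An ICC of 0.01 gives type I error 13.9% (14.3% by simulation) and CI coverage 86.1%. An ICC of 0.05 gives 37.8% (38.0% by simulation) and coverage 62.2%.

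**Size if the two clinics are treated as fixed.** A non-programme difference δ is then a bias. With no programme effect, the chance of significance is Φ(δ/0.0653 − 1.96) + Φ(−δ/0.0653 − 1.96):

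- δ = 0.05 z: 12%
- δ = 0.10 z: 33%
- δ = 0.13 z: 51%

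**Example of a tipping value.** If the estimate equalled the design difference of 0.2 z, the near limit of the planned interval would lie 0.2 − 0.128 = 0.072 z from zero. A clinic difference of about 0.07 z in the same direction would remove significance.

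**The case against.** The strongest reply is that this is a disclosed constraint. The article calls the design quasi-experimental, names the two communities, explains why neither individual nor group randomisation was used, and states that the populations are demographically similar. Limitations and sensitivity analyses are often left to the full protocol, the analysis plan or the results paper. This stands as far as it goes: nothing is concealed, and a non-randomised design is a legitimate choice in this setting. But disclosing that allocation was not random does not change the label on T, what its interval covers, or the stated aim. Similar demographics do not establish similar 6-month courses.

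A second reply is that the size is assumed. That is also true. No between-clinic SD or ICC appears in the article, and treating two chosen clinics as draws from a population of clinics is itself a modelling choice. The fixed-difference figures avoid that choice, but they too depend on an unknown quantity. The inseparability of clinic and programme needs no such assumption.

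Three stronger readings are tempting, and the documents do not support them.

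- **The trial can say nothing about effectiveness.** An estimate of 0.2 z would still be 0.2/0.078 = 2.6 total SEs from zero at τ = 0.03 and 0.2/0.096 = 2.1 at τ = 0.05. It falls below 1.96 only at τ = 0.08, where 0.2/0.131 = 1.5.
- **Any small community difference would produce significance.** A difference of 0.05 z does so about 12% of the time. It takes about 0.13 z, roughly two thirds of the design difference, to do so half the time.
- **The advisory boards' systems-change work favours one arm.** The CBPR approach section describes this work as county-wide, and both communities lie in the same county. It shows no difference between arms. Differences in enrolment season or referral habits are not documented either.

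**Conclusion.** The point holds as a matter of labelling, inference and conclusion. With one clinic per arm, T is the programme effect plus any clinic difference in 6-month BMI z given baseline. Its test and interval understate uncertainty about the programme effect by an amount that this trial cannot estimate. This follows from the design and model as written.

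Only the size rests on assumptions: residual SD 0.4, 75 completers per arm, a two-sided test, and either an assumed between-clinic SD or an assumed fixed difference. Over the illustrative ranges, the nominal 5% error becomes about 10% to 33% for between-clinic SDs of 0.03 to 0.08 z, or about 12% to 51% for fixed differences of 0.05 to 0.13 z. These figures illustrate sensitivity and do not estimate what will happen in these two clinics. The primary conclusion should be reworded and bounded; the design need not be abandoned.

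**What to change.** In the Primary analysis section:

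1. Describe T as the baseline-adjusted difference in 6-month BMI z between the two clinics, not as the intervention effect without qualification.
2. Limit the primary conclusion to that two-clinic contrast, and say that attributing it to the programme assumes no other clinic difference in 6-month BMI z given baseline.
3. Pre-specify a sensitivity analysis that reports the estimate and its CI over a stated range of clinic differences (or between-clinic SDs), including the difference that would remove significance. Fix the range before outcome data are examined.

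Optionally, if records allow, report beside the primary estimate the 6-month BMI z trend by clinic in eligible children who did not enrol. The Study setting section says the health centre "is the medical home for 91% of all children" in the county, and the Data management section shows that it records heights and weights electronically. The article does not show that non-enrolled children have two measurements six months apart, or that their trends resemble those of enrolled children. This would therefore be a supporting check only, reported with its limits: selection, missing visits and less standardised measurement.

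**Cost.** Items 1 to 3 need only wording and a short calculation. The price is wider intervals in the sensitivity analysis and a more cautious conclusion. The optional check would need a de-identified record extract and an ethics amendment.

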#### CBPR approach

This study uses a Community-Based Participatory Research (CBPR) approach fostered by over 20 years of academic-community partnership between the FQHC and their academic partners at a nearby university [31]. CBPR is the co-construction of research through partnerships between researchers and the people affected by, or responsible for, action on the issue under study. Some of the benefits of participatory approaches include the creation of culturally and logistically appropriate research, enhanced recruitment, increased stakeholder capacity, improved sustainability of project goals, and greater potential for systems change [32, 33].

The collaborative and participatory evaluation methods in La Vida Buena includes engagement of a community advisory board (CAB) and a participant advisory board (PAB). The CAB provides support for project development, resources, recruitment and intervention activities. The CAB includes partners from organizations throughout the county, including a biking nonprofit, representatives from local schools, the cooperative extension, and the local farmer’s market. The participant advisory group (PAB) is comprised of parents who have completed the program and who provide the perspective of parents with young children in project planning and dissemination.

Both the CAB and the PAB are active in community- and systems-change activities to complement the emphasis on family behavior change in La Vida Buena. It is essential to integrate clinical and community systems to address childhood obesity [16]. The La Vida Buena team works with the CAB and PAB to identify systems and policy changes that foster a healthy environment in the county.

### La Vida Buena intervention

#### Intervention development

La Vida Buena was adapted from a program that the FQHC originally delivered to adolescents 10–19 years old; parents were invited but not required to participate. An initial pilot adoption and preliminary evaluation of the program using pre- and post-tests showed statistically significant improvement in nutrition-related health behaviors, including decreased consumption of sugar-sweetened beverages (SSBs) and fast food consumption and increased fruit and vegetable consumption.

In the current La Vida Buena Program, the FQHC adapted the program for younger children in order to intervene at an earlier age and implement a more rigorous evaluation framework. The FQHC leadership decided to implement the intervention with a younger population because the proportion of children with overweight and obesity increases steadily through the childhood and teenage years [34, 35]. Early intervention is critical to prevent the physical and psychosocial effects of overweight and obesity. This program focuses on a family-based strategy as a way to shape behaviors in the home, which are key risk factors for developing overweight and obesity [36]. LVB is designed to target key family behaviors that will shape the child’s diet and physical activity habits at a crucial time.

The LVB team used the structure of the original program to design a curriculum geared towards children 5–8 and their parents. The FQHC piloted the curriculum and refined the intervention based on feedback from the CHWs, observers and participants. Revisions included ensuring that the language was regionally appropriate, that activities engaged both children and parents, that the discussion included both parents and children, and that physical activity was age-appropriate.

In the curriculum design, the FQHC and academic partner carefully considered language and framing. While we recognize that childhood overweight and obesity has serious health implications that last throughout the life span, the La Vida Buena program focuses on a healthy diet, behavior change for a healthy home environment, and positive aspects of a healthy lifestyle, rather than weight or the negative consequences of overweight and obesity.

